#### Recruitment

We will purposively sample clinicians to ensure we capture a broad and multidisciplinary range of perspectives [28]. The project officer will approach the clinicians via email or in person during clinic visits. All participants will be advised (verbally and in writing) that participation is voluntary and they are able to withdraw from the study at any point without reason or consequence. The potential participants will be provided with the study information sheet and consent form. If the participant has consented to take part in the study, the researcher will administer the questionnaire in person or will send a link to the questionnaire. At the end of the questionnaire, participants will have the option of consenting to participate in the focus groups. Clinicians will then be contacted by phone or email by the project officer to invite them to attend a focus group. It is estimated that 15–20 clinicians will take part in a focus group. This number is feasible based on previous studies of clinician views of PWMS [32, 33].

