### Part 2: Assessment of clinician views of secondary services for children who are above their healthy weight range

In part 2 of the study clinician views of the PWMS they work in, the service they provide and their experience working in that service will be assessed by questionnaire and focus groups. The following information will be collected: 1) staffing mix; 2) expertize; 3) training; 4) time commitments; 5) service model; 6) level of multi-disciplinary team work; 7) internal and external department links; 8) costs and funding sources.

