#### Participants

Participants will be clinicians who are involved with the care of patients in a secondary or tertiary PWMS. Clinicians will include pediatricians, dietitians, nurses, psychologists and physiotherapists. Clinicians will be given a patient information sheet and written consent will be obtained before taking part on the study.

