##### Quantitative data

A questionnaire, developed by the multi-disciplinary research team and clinical team, will be used to capture clinician views about their PWMS. The questionnaire is based on a previously published survey [19]and includes questions on respondent demographics and experience in pediatric weight management, clinic levels of service and demands, weight management service model, approaches to weight management. The questionnaire will take no longer than 20 min to complete.

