#### Data analysis

Data analysis will be performed using appropriate statistical software. Data will be presented descriptively including frequency distributions. Differences in parental and clinician satisfaction between models of care will be examined by comparison of means (continuous data) or Chi-squared (categorical data). Effectiveness of each model of care will be determine by change in BMI z-scores, expressed as a continuous variable and categorical variable (change ≤5% or > 5%), from baseline to 3 and 6 months. Weight changes in children with obesity are associated with change in metabolic outcomes [38]. Predictors of effectiveness, including models of care, eating behaviors and physical activity, will be examined by modelling.

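### Clinicians are purposively selected before the questionnaire, yet clinician satisfaction is to be tested between models of care, so differences may reflect who was selected

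*Protocol article*

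**What the plan says.** The Recruitment section of Part 2 opens with the sampling method: "We will purposively sample clinicians to ensure we capture a broad and multidisciplinary range of perspectives". It then describes approach by email or in person, information and consent, and a questionnaire given in person or by link. The focus-group step comes after that: "At the end of the questionnaire, participants will have the option of consenting to participate in the focus groups".

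On eligibility, the Part 2 Participants section says: "Participants will be clinicians who are involved with the care of patients in a secondary or tertiary PWMS". It names five disciplines: "Clinicians will include pediatricians, dietitians, nurses, psychologists and physiotherapists".

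The Part 2 Quantitative data section says that the questionnaire covers the respondent's background and experience, and also "clinic levels of service and demands, weight management service model, approaches to weight management".

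The Data analysis section of Part 4 states the use: "Differences in parental and clinician satisfaction between models of care will be examined by comparison of means" for continuous data, with Chi-squared for categorical data. The Study setting section gives six secondary clinics and one tertiary clinic, each with a different model of care.

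**The concern.** Purposive sampling suits qualitative work, where the aim is to hear a wide range of views. A comparison of means or proportions between groups needs something else: the respondents in each group should stand for that group, or at least should not have been chosen by a process that can differ between groups. The protocol uses the first kind of sample for the second kind of analysis.

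Model and clinic coincide here, so a between-model comparison of clinician satisfaction is a comparison between small sets of staff at individual clinics. If the choice of whom to approach differs from clinic to clinic, in discipline or in known attitude to the service, that choice is built into the contrast. The Study activities section assigns Parts 1, 2 and 3 to the primary objective, which includes the acceptability of the different models, so the comparison bears on the study's main question.

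**Working it through.** The plan gives no figure for this point that could be reproduced: no questionnaire sample size for clinicians, no staff numbers per clinic and no assumed effect. The check is therefore a reading of the sections against each other.

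**1. At which stage does the selection act?** In Part 2, Recruitment, the order is purposive sampling, approach, consent, questionnaire, option to join a focus group, invitation to a focus group. Focus-group members are thus an opt-in subset of questionnaire completers, and the purposive step lies upstream of both. The only stated aim of the selection is breadth and mix of disciplines; balance or coverage by clinic or model is not part of it.

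**2. How are parents handled?** In Part 1, Recruitment, eligible parents are approached at clinic visits and complete the questionnaire. Maximum variation sampling is mentioned only afterwards, for the one-on-one interviews. The protocol therefore already has a design in which selection for variety is kept to the qualitative stage. Part 2, as written, departs from it.

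**3. Do the questionnaire data feed the comparison?** Part 4, Data analysis, names clinician satisfaction as a variable compared between models. The clinician questionnaire of Part 2 is the only quantitative clinician instrument described. Its listed content includes no item called satisfaction, so the link is an inference, but no other source is offered.

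**4. What does selection do to the contrast?** Let μ_c be the mean response of all eligible staff at clinic c, and let b_c be the amount by which the mean of those selected departs from it. The planned comparison of clinics 1 and 2 then estimates

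(μ_1 + b_1) − (μ_2 + b_2) = (μ_1 − μ_2) + (b_1 − b_2).

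The second term vanishes only if selection shifts both clinics equally. It has two sources:

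- the disciplines selected at a clinic may be in different proportions from its staff;
- within a discipline, the persons selected may differ from their colleagues.

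A larger purposive sample chosen in the same way does not remove it. If every eligible clinician is invited, the investigators' choice no longer contributes to b_c and only non-response does.

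**5. Can b_1 − b_2 be sized?** No. The one clinician number in the document, 15–20, is an estimate for the focus groups. Because these are drawn from questionnaire completers, it is a lower bound for the questionnaire if that estimate is met. It says nothing about how far the selected staff differ from the rest.

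**The case against.** The strongest reply is that the purposive sentence may only state the qualitative aim. The Part 1 wording for the parent interviews is very similar and rests on the same reference, and an article condenses a full protocol in which the sampling frame may be set out. This is possible, but the article places the sentence ahead of the questionnaire, and a reader following it would select first. If the intention was otherwise, the correction is even simpler.

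Other parts of the reply stand, and they limit what can be claimed:

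- A reader might infer that a clinic could be left out, or that the sample could come from one clinic. The Methods part of the Abstract says participants are recruited from seven services and lists clinicians among them. No quota per clinic is set, but the document does not support predicting an empty clinic.
- A reader might set 15–20 clinicians against the combinations of seven clinics and five disciplines and call coverage poor. That uses a focus-group number for the questionnaire and assumes that every clinic employs all five disciplines. The Background says services vary with resourcing and staff expertise. Probabilities based on random draws do not fit either, since purposive selection is not random.
- A reader might see a contradiction between open eligibility and selective recruitment. The Participants section does not say that all clinicians are included.
- A reader might extend the problem to the whole description of each model. Only satisfaction is named for the between-model comparison. Facts such as staffing and service model can come from one well-informed staff member, and managers, financial records, parents and routine data on all attending children also contribute.

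It is also true that inviting everyone does not make clinics alike in discipline mix.

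**Conclusion.** The point holds in a limited form. As written, the clinician questionnaire is answered by a purposive sample, and the clinician responses are then to be compared between models by means or Chi-squared. A difference found this way may reflect who was selected as well as the model. The mismatch does not depend on the number of respondents and would disappear only if all eligible clinicians were in fact approached.

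The conclusion rests on two readings: that the purposive sentence governs the questionnaire, as its position indicates, and that the satisfaction data come from that questionnaire. The bias cannot be quantified from the document, and its direction is unknown. The effectiveness comparison in Part 4, which uses routine data on all attending children, is not affected. The change should be made because it concerns a planned test under the primary objective and costs almost nothing.

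**What to change.** In Part 2, Recruitment, state that every eligible clinician at each of the seven services is invited to complete the questionnaire, using the link already planned, and that the numbers invited and responding will be reported by clinic and discipline. Move purposive sampling to the next step, the choice of focus-group members from among completers, with clinic and discipline as its dimensions. This matches the order already used for parents in Part 1.

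If purposive selection is to be kept for the questionnaire, amend Part 4, Data analysis, so that clinician results are described by model and not tested.

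In either case, acknowledge that non-response and real differences in discipline mix between clinics can still influence the comparison.

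The cost is a change of wording and a few more invitations to a questionnaire of at most 20 minutes. No new instrument or visit is needed.

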### Part 3: Health service manager views of secondary weight management services for children who are above their healthy weight range.

Part 3 of the study is a qualitative investigation of the views of health service managers of the implementation of PWMS.

#### Participants

Health Service Managers who manage health services that have a secondary or tertiary PWMS. Appropriate Health Service Managers will be recruited via email and will be given a patient information sheet and consent form for written consent.

#### Qualitative data

One-on-one interviews, using semi-structured interviews will be used to assess the views of health service managers. 1) LHD views of the PWMS; 2) future plans for the service; 3) funding considerations; 4) linkage and integration with related services; 5) perceptions of strengths and weaknesses of the pediatric weight management service; 6) barriers and enablers; 7) recommended resources; 8) recommendations for improvement for future PWMS.

#### Recruitment

Health Service Managers who meet the inclusion criteria will be identified by the primary investigators at each site. The project officer will approach the Health Service Managers via email. The researcher will then book in a time to conduct the one-on-one interview either in person or via the telephone at a time that suits the participant.

### Part 1, 2 & 3 qualitative data analysis

Responses from the focus groups/ one-on-one interviews will be recorded on a high-quality recorder and the interviews will be transcribed verbatim by an independent researcher. Two investigators will listen to the interviews and brief synopses of the emergent themes raised in each focus group/ interview will be prepared. Each transcript will then be coded by one of the investigators experienced in qualitative research methods using the qualitative data analysis software package, NVIVO 11 (QSR International PTY LTD). We will conduct content analysis of the qualitative data and the conceptual frameworks of Miles and Huberman (1994) [34] will be used to guide data analysis.

A random sample of 20% of the transcripts will be independently coded and cross checked for inter-rater reliability. Once coding is complete, the coders will meet to review the coding and address any coding disagreements. If the coding pair cannot agree on how to code a particular passage, the issue will be referred to the project manager. If the larger group cannot resolve the problem, the passage will be omitted from the analysis. This multilevel consensus coding method has been applied in multiple settings and meets accepted standards of reliability and validity in qualitative research [34]. The final coding will be analyzed and key response categories will be identified and enumerated [34]. The reporting of the results of the qualitative data collection and analysis will be guided by the COREQ criteria [35].

### Part 4: Efficacy of Services for Children Attending Secondary Weight Management Services

Part 4 is an audit of clinic notes and medical records of data collected routinely as part of standard clinical care for pediatric weight management.

Part 4 will address the following objectives:

Secondary objective: To compare the clinical effectiveness of the different models of care for the management of childhood obesity.

Secondary objectives: To assess the impact of the different pediatric weight management models of care on weight-related behaviors (eating, physical activity and sedentary behaviors).

#### Participants

All children attending the weight management clinics will be included in part 4 of the study.

#### Data collection

The Healthy Lifestyle Questionnaire was developed for the collection of routine clinical data. This questionnaire includes selected validated questions from the NSW Population Health Survey [36] and the NSW Schools Physical Activity and Nutrition Survey [37]. The questions include data on participants’ demographics, screen time, moderate to vigorous physical activity per day, water consumption, milk consumption, sugary drink consumption, breakfast consumption, consumption of some specific snacks, fruit and vegetable consumption and sleep time. Clinicians complete a section on the patient’s height, weight and co-morbidities as part of routine clinical care. These data will be collected at baseline and at three and six months.

#### Data analysis

Data analysis will be performed using appropriate statistical software. Data will be presented descriptively including frequency distributions. Differences in parental and clinician satisfaction between models of care will be examined by comparison of means (continuous data) or Chi-squared (categorical data). Effectiveness of each model of care will be determine by change in BMI z-scores, expressed as a continuous variable and categorical variable (change ≤5% or > 5%), from baseline to 3 and 6 months. Weight changes in children with obesity are associated with change in metabolic outcomes [38]. Predictors of effectiveness, including models of care, eating behaviors and physical activity, will be examined by modelling.

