**Methods:**

This is a acceptability and effectiveness study building upon existing and planned secondary and tertiary level service delivery in several health districts. This study will recruit participants from seven different pediatric weight management services (PWMS) across five Local Health Districts in NSW, Australia. Using a mixed-methods approach we will document a range of process, impact and clinical outcome measures in order to better understand the context and the effectiveness of each PWMS model. The project development and implementation is guided by the Theoretical Domains Framework. Participants will include parents of children less than 18 years of age attending PWMS, clinicians working as part of PWMS and health service managers. Data will be captured using a combination of anthropometric measures, questionnaires, one-on-one semi-structured interviews and focus groups.

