## Background

Pediatric obesity is a serious, but clinically neglected, chronic health problem. In Australia one in four school-aged children and adolescents is affected by overweight [1] or obesity (6% with obesity, a further 2% with severe obesity) [2]. Pediatric obesity is associated with a range of immediate and longer-term health problems [3]. Despite the high prevalence, excess weight problems are infrequently managed when children attend clinical services [4, 5]. Barriers to weight management by health professionals include: difficulty raising the issue, uncertainty about advice to offer and referral pathways, and lack of local service capacity [5, 6].

Untreated, the natural history of obesity in children and adolescents will worsen over time [7]. The American Academy of Pediatrics recommends that obesity treatment uses a “chronic-care” approach to management, with different types and intensity of treatment dependent upon severity of obesity [8]. Family-based lifestyle interventions incorporating behavior modification around eating and activity are effective and considered first-line treatment for pediatric obesity [3, 9, 10], especially in younger children [11]. Although there is a central role for primary care physicians and other health professionals, including nurses and dietitians, in the management of childhood overweight and obesity [12], there is also a need for specialist secondary and tertiary care services for those with more severe obesity [3]. Primary, secondary and tertiary care services can all provide dietary modification, advice about exercise and physical activity [12], medical management of obesity-associated complications, family-based lifestyle changes and behavior modification techniques [3]. Secondary and tertiary services differ from primary care services by providing more intensive services within a multi-disciplinary team environment and for children with more severe obesity.

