Australia has a publicly funded healthcare system [13]. The individual states and territories are responsible for managing hospital and community services [14]. Primary care is the first contact with the health system and does not include hospital services. Secondary care services are provided by specialist care providers and are a direct link between primary and tertiary services. Within New South Wales the state is divided into eight metropolitan local health districts (LHDs) and seven rural LHDs. In addition, there are two specialist networks, including the Sydney Children’s Hospitals Network (SCHN).

There are limited pediatric obesity services in Australia, including in the state of NSW. Prior to 2017, the number of services available in the secondary and tertiary setting had not changed in the previous ten years [15], despite the number of children with severe obesity significantly increasing. The few existing services are poorly linked, with no well-established models of care or healthcare pathways across primary, secondary or tertiary care networks. Adequate treatment strategies for childhood obesity will require changes in healthcare delivery systems [16].

Several LHD’s within NSW are implementing new services to deliver integrated weight management programs for children and adolescents. The new and existing services vary greatly in their models of care, depending upon local resourcing, clinical needs, staff expertise and patient characteristics. We have a unique opportunity to research the implementation and integration of these pediatric weight management services (PWMS) alongside established services to determine the acceptability, clinical effectiveness and impact of the services. There is limited research assessing the effectiveness of interventions in clinical practice for children with obesity [17] . Inadequate documentation and poor retention rates of patients are factors shown to prevent the assessment of “real-world” models of care for PWMS in international settings [17]. No such research has been undertaken previously in Australia.

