### Study setting

The study will be undertaken at six secondary level care clinics and one tertiary clinic for child weight management. These clinics are limited to children less than 18 years of age and their families. Each clinic uses a different model of care with a combination of face-to-face and group education sessions within a multi-disciplinary team.

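### With one model of care per clinic and no randomisation, the planned comparisons cannot attribute differences in satisfaction or BMI z-score change to the model of care

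*Protocol article*

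**What the plan says.** **Design.** The protocol article's Study setting section says "The study will be undertaken at six secondary level care clinics and one tertiary clinic for child weight management", and adds "Each clinic uses a different model of care". The abstract counts "seven different pediatric weight management services (PWMS) across five Local Health Districts in NSW, Australia". The Recruitment section of Part 1 calls the study non-randomised, and Methods/design presents it as a natural experiment.

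**Expected differences between services.** The Background says "The new and existing services vary greatly in their models of care, depending upon local resourcing, clinical needs, staff expertise and patient characteristics". It also says that family-based lifestyle treatment is effective, "especially in younger children".

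**Objectives.** Acceptability and retention across models form the primary objective. Comparing the models' clinical effectiveness and their impact on eating, activity and sedentary behaviour are secondary objectives.

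**Analysis (Part 4, Data analysis).** Differences in parent and clinician satisfaction between models "will be examined by comparison of means (continuous data) or Chi-squared (categorical data"). For the clinical outcome, "Effectiveness of each model of care will be determine by change in BMI z-scores", taken from baseline to 3 and 6 months both as a continuous variable and split at 5%. A last sentence plans modelling of predictors of effectiveness and names three: model of care, eating behaviours and physical activity.

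**Use of the results.** Part 5 carries BMI z-score differences into cost-effectiveness ratios for each model. The Discussion expects the findings to guide service planning and to show managers which models may suit their region.

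**The concern.** The plan compares models, but its data can only compare clinics. Each model is seen in a single clinic, with that clinic's staff, catchment and patients. The protocol itself links patient mix to the model offered and links age to treatment response, which are the two conditions for confounding.

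As written, the analysis does little to counter this. Satisfaction, which serves the primary objective, is tested without adjustment. The BMI z-score modelling names no baseline patient characteristic. Its two named predictors other than model of care are behaviours that the services are meant to change.

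At stake is the interpretation. A service with younger or less severely affected children could be reported as running a better model, and that reading would pass into the cost-effectiveness ratios and the planning advice.

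**Working it through.** **1. The plan's own figure.** The only sample size is 140 parent questionnaires. It is described as pragmatic and has no alpha, power, effect size, SD or intraclass correlation (ICC), so there is nothing to reproduce. It is used here only as 140/7 = 20 parents per clinic, which assumes an even spread.

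**2. Model against clinic.** Inputs from Study setting: 6 + 1 = 7 clinics and 7 different models. Degrees of freedom for clinic within model = 7 − 7 = 0. A clinic mean is the sum of a model effect, a clinic effect and a case-mix effect. With one clinic per model the first two cannot be separated. Neither a clinic random effect nor a cluster-robust variance changes this. Tertiary against secondary leaves one clinic on one side. New against existing, the contrast used in Part 5, might put several clinics in each group, but the split is not given.

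**3. Case-mix (assumed inputs).** Gap between two identical models = difference in the share of younger children × difference in mean change.
- Shares 70% and 30%, mean changes −0.20 and −0.05: (0.70 − 0.30) × (−0.20 + 0.05) = 0.40 × (−0.15) = −0.06 BMI z.
- Half that imbalance: 0.20 × (−0.15) = −0.03.

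Severity affects the 5% split in the same way, if 5% means 5% of baseline BMI z-score. A fall of 0.12 is 0.12/2.0 = 6.0% at baseline z 2.0 but 0.12/3.5 = 3.4% at baseline z 3.5, so the same fall lies on opposite sides of the cut.

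**4. The named predictors.** Eating and physical activity come from a questionnaire given at baseline, 3 and 6 months, and changing them is a secondary objective. Baseline values would be ordinary covariates. Follow-up values would be mediators: adjusting for them removes part of the service effect and leaves age and severity uncontrolled. The plan does not say which are meant. Demographics, height, weight and co-morbidities are collected (Part 4, Data collection), and a BMI z-score already requires age and sex.

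**5. Retention (assumed inputs).** If children who stay change by −0.15 and those who leave by 0, the mean over all children is −0.15 × retention:

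| Retention | Children who stay | All children |
|---|---|---|
| 90% | −0.15 | −0.135 |
| 70% | −0.15 | −0.105 |
| 50% | −0.15 | −0.075 |

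Services with quite different overall results would look alike among attenders.

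**6. Tests on individuals (assumed ICC).** This step applies only if a result is read as the effect of a model beyond the clinic that ran it. Design effect = 1 + (m − 1) × ICC with m = 20; actual error of a nominal 5% two-clinic test = 2 × [1 − Φ(1.96/√DE)].
- ICC 0.02: DE = 1.38, error 9.5%.
- ICC 0.05: DE = 1.95, error 16.0%.

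A t test with the exact variance inflation 1 + m × ICC/(1 − ICC) gives 9.6% and 16.6%. Over ICC 0.01 to 0.10 that t test gives 7% to 27%, and the standard error of a two-clinic difference should be 1.10 to 1.80 times as large.

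**The case against.** The strongest reply is that the plan is not as bare as its first sentences suggest. Multi-predictor modelling of effectiveness is planned with model of care as a predictor, and its wording does not close the covariate list. An article may leave covariates, model form and missing-data handling to a full protocol or SAP. The study openly calls itself non-randomised, clinical effectiveness is secondary, and retention is itself an outcome to be assessed.

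Much of this stands, and it rules out several stronger readings that a reader might infer:

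- **That BMI z-score change is compared only in raw form.** It is not, given the planned modelling. Only the satisfaction comparison is unadjusted as written.
- **That the standard errors are too narrow in general.** Ordinary standard errors properly describe these seven clinics. They are too narrow only for claims beyond those clinics, and adjusting for covariates would not widen them to cover clinic-to-clinic variation. Only restating the claim answers this.
- **That follow-up is known to be missing in a model-dependent way.** This is partly inference. Part 4 audits routine notes, Part 1 indicates that programmes differ in length, and the Background names poor retention as a threat, but no rate or pattern is given.
- **That the figures above measure the bias.** They rest on assumed inputs and show what could happen, not its size here.

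The reply does not reach the one-model-per-clinic structure. No SAP can supply degrees of freedom that the design lacks, and the article itself states the comparison as one of models.

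**Conclusion.** The concern holds in a limited form. With seven clinics, seven models and no randomisation, neither satisfaction nor BMI z-score differences can be attributed to model of care. That conclusion needs only the documents' own counts. That case-mix is a credible alternative explanation also follows from the documents, since the Background ties patient characteristics to the model and age to response.

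The size of the distortion is unknown. The 0.03 to 0.06 z gap depends on assumed age mixes and responses. The error rate of about 10% to 16% for two clinics of 20 depends on an assumed ICC of 0.02 to 0.05 and on generalising beyond the clinics studied. The absence of a full covariate list or missing-data method from an article is not in itself a fault.

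**What to change.** Revise the Data analysis section of Part 4 as follows.

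- **Claim.** Report results as differences between services with confidence intervals. Discuss model features, such as tier, intensity, group or individual delivery, and new or established, descriptively and not as tested model effects.
- **BMI z-score.** Fit the 3- and 6-month values in one repeated-measures model (service × time), adjusted for baseline BMI z-score, age, sex, co-morbidities and the demographics collected. Include every child with a baseline and at least one follow-up value. Do not adjust the service comparison for follow-up eating or activity.
- **Retention.** Report it per service. Add a sensitivity analysis for children without follow-up, for example counting them as non-responders in the categorical analysis. That is a strong assumption, so it should not be the main analysis.
- **Parent satisfaction.** Adjust for the child's age, sex and severity where these can be linked to Part 4 records or are asked in the Part 1 questionnaire.
- **Clinician satisfaction.** Keep it descriptive, since child covariates have no meaning there.

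**Cost.** For BMI z-score this changes wording and analysis only, with data already due to be collected. For parent satisfaction it needs a linkage that the article does not describe, or a few added questions. Unmeasured confounding remains, the repeated-measures model assumes data missing at random, and claims about models become more modest.
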